### Health economic analysis

Detailed information on all resources required for both arms, including family born costs, productivity losses and/or out of school days for children, and costs from the health provider’s (NHS) perspective will be collected. Secondary care resource use will be collected from hospital records. Resources identified will be costed using appropriate local and national unit cost data to provide estimates of the cost incurred during the intervention.

The preference-based generic Health Related Quality of Life (HRQoL) measures CHU-9D for children and EQ-5D for adults will be used to enable estimation of QALYs for both arms. The sensitivity of these measures will be compared to other disease specific outcomes within the trial. Missing data will be examined as to whether cases with missing data are similar to those with full economic data in a similar manner to the main trial analysis.

Descriptive statistics will be presented for main cost outcomes and HRQoL measures in terms of QALYs; at each occasion inferences will be made and conclusions will be drawn, allowing identification of the best way of measuring and collecting data for the full cost-effectiveness analysis within further trials.

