### Sample size

This study consists of two separate and independent cohorts. The first cohort will consist of 30 children (aged 8–16 years) randomised 1:1 to either APAP or standard of care. The second cohort will consist of 30 adults (aged ≥ 16 years) randomised 1:1 to APAP + standard care or standard care alone. Each cohort represents an independent trial with 90% power to detect a difference in cancellation rate at a significance level of 0.05. Since the cohorts are independent and each has a type I error allocation of 5%, no adjustments for multiple comparisons are needed. Any analyses pooling the child and adult cohorts will be considered exploratory.

In the previous pilot study in children, the results of the cancellation task within each subject group were normally distributed with standard deviation 2, resulting in a mean score difference between APAP treatment and standard care at six weeks of 2.6. Based on this finding, 24 evaluable participants (in each cohort) will provide 90% power to detect a difference in the primary outcome of 2.6 while preserving a significance level of 0.05 (two-sided). This calculation assumes that there is a moderate correlation of 0.5 between the baseline and follow-up measures, and accounts for model adjustment for baseline score [45]. Allowing for 20% withdrawal/loss-to-follow-up, a sample size of 30 individuals randomised 1:1 into two groups will have > 90% power to detect a difference of 2.6 points in cancellation using an analysis of covariance (ANCOVA) model to adjust for the baseline cancellation measure and minimisation factors. The same design characteristics will be used for the adult cohort and the child cohort. Though the values used in the sample size calculation were derived from a cohort of children, no pilot data for adults are available, and the mechanisms by which the treatment effect may be different for adults and children are currently unknown.

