### Outcomes

The primary outcome is change from baseline to six months post randomisation in cancellation, a measure of visual attention and processing speed. Secondary outcomes are changes in cognition, pain intensity, quality of life, daytime oximetry, brain MRI and cardiac investigations. Health economic measures will determine quality of life measures in quality-adjusted life years (QALY) terms and the main cost drivers in terms of therapy resources, equipment and travel, etc., and any change in use of other resources, e.g. requirement for transfusion, opioids, other pain relief and hospital admissions to provide a preliminary estimate of the cost of overnight respiratory support compared to standard care. AEs and evidence of bone marrow suppression are key safety outcomes.

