### Data collection

Data collection is summarised in Fig. 1. Baseline assessments include demographics, medical history, concomitant medications, physical examination, sleep habits, [46] Epworth Sleepiness instrument [47] and measurements of pain burden [48] and daily pain as well as quality of life using the CHU-9D21 in children [49] and the Euroqol EQ-5D22 in adults [50] as well as the sickle module of the PEDS-QL [51]. Physiologic tests at baseline include a brain MRI and overnight oximetry, which are required for minimisation, as well as daytime oximetry and laboratory measures. The baseline cognitive outcomes assessment is also required before randomisation. Whenever possible, investigators are encouraged to perform heart MRI, echocardiography and a 6MWT.

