**Fig. 2 Fig2:**
[figure not shown]
Study flow

At the end of the trial (month 6), participants will undergo end of study tests, including blood and urine tests, medical review, review of adherence and AEs, quality of life, executive function testing and MRI of the brain unless contraindicated. Whenever possible, echocardiography, a 6MWT and heart MRI will also be performed.

Data will be collected on paper case report forms to be stored in a locked cabinet and later double-entered into data management software password-protected and stored securely.

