### Statistical analysis

Analyses will be performed in accordance with the intention-to-treat principle, though a ‘per-protocol’ subgroup with adequate treatment adherence will be defined before database lock. The primary analysis of change in cancellation time will be based on an ANCOVA model containing the baseline cancellation score and minimisation factors as fixed covariates. A sensitivity analysis excluding the minimisation factors will also be performed. Pre-specified subgroups include the minimisation factors and the subgroup of individuals with adequate APAP compliance on the night before cognitive testing. Continuous variables that are collected at baseline and six months will be analysed using similar models. Pain and other outcomes with multiple collection points will be analysed using mixed models for repeated measures, based on observed data and including the fixed, categorical effects of treatment, minimisation factors, visit and treatment-by-visit interaction, as well as the continuous, fixed covariates of baseline and baseline-by-visit interaction. An unstructured covariance will be used to model the within-patient errors if possible; compound symmetry will be used otherwise. Binary outcomes will be analysed using logistic regression, including the minimisation variables as fixed covariates.

The overall significance level of 5% will be allocated for the primary analysis. Type 1 error adjustments for secondary outcomes will not be made and analyses beyond the primary outcome should be interpreted with caution.

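### QALYs by arm are summarised descriptively and conclusions drawn from them, without using the baseline utility that the trial collects; the raw comparison is unbiased but less precise than it need be

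*Protocol article*

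**What the plan says.** All references are to the protocol article.

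- **Health economic analysis.** CHU-9D (children) and EQ-5D (adults) "will be used to enable estimation of QALYs for both arms". The only method named is this: "Descriptive statistics will be presented for main cost outcomes and HRQoL measures in terms of QALYs". The same sentence goes on: "at each occasion inferences will be made and conclusions will be drawn". Its stated purpose is to learn how best to measure and collect data for a full cost-effectiveness analysis in later trials. No QALY formula, between-arm QALY model or QALY interval is given.
- **Data collection.** CHU-9D and EQ-5D are among the baseline assessments. At month 6 the end-of-study tests include "review of adherence and AEs, quality of life, executive function testing and MRI of the brain unless contraindicated". The text mentions no utility measurement in between (Fig. 1 is not shown).
- **Statistical analysis.** The primary model is an ANCOVA with baseline score and minimisation factors. "Continuous variables that are collected at baseline and six months will be analysed using similar models".
- **Outcomes.** The economic measures are meant "to provide a preliminary estimate of the cost of overnight respiratory support compared to standard care".
- **Methods and design; Sample size.** The child and adult cohorts are analysed separately, each with 30 randomised 1:1 and 24 evaluable.

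**The concern.** The general ANCOVA rule applies to variables measured at both baseline and six months. It therefore reaches the CHU-9D and EQ-5D scores. A QALY accrues over the whole period and has no baseline value of its own, and the health economic section gives it a separate, descriptive treatment. The rule does not clearly reach it.

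If QALYs are computed as area under the curve, baseline utility is one of the quantities being summed. An arm that happens to start with better utility then shows more QALYs whatever the treatment does. With 12 to 15 people per arm in each cohort, such differences can be as large as a plausible effect. Two risks follow:

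- The raw QALY comparison is noisier than it need be.
- The same questionnaires can yield an adjusted utility effect and a raw QALY difference that point in different directions, with nothing in the article to say which supports a statement about QALY gain or loss.

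**Working it through.** **The plan's own figure.** The article gives no precision for QALYs; its only sample-size figure concerns cancellation: "24 evaluable participants (in each cohort) will provide 90% power to detect a difference in the primary outcome of 2.6". With SD 2, difference 2.6, correlation 0.5 and two-sided 0.05, the ANCOVA residual SD is 2 × √(1 − 0.25) = 1.732. This needs 10 per arm by the normal approximation or 11 by the t distribution. Twelve per arm gives about 94% power, and 24 / 0.8 = 30. The stated size holds and this point does not affect it. It supplies the group sizes used below, 12 to 15 per arm.

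**Inputs that are assumptions.** The documents give no QALY formula, utility SD or utility correlation. I assume a two-point area under the curve over half a year:

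QALY = 0.5 × (u0 + u6)/2 = 0.25 × (u0 + u6),

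where u0 and u6 are the utilities at baseline and month 6, ρ is their correlation, and k = SD(u0)/SD(u6). The only correlation stated, 0.5, is for cancellation, so I show a range.

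**Variance of the arm difference**, n per arm, SD(u6) = s:

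- Raw: 0.0625 × (2/n) × s² × (k² + 1 + 2ρk)
- Adjusted for u0: 0.0625 × (2/n) × s² × (1 − ρ²)
- Ratio: (k² + 1 + 2ρk)/(1 − ρ²), which is 2/(1 − ρ) when k = 1

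| | ρ = 0 | ρ = 0.3 | ρ = 0.5 | ρ = 0.7 |
|---|---|---|---|---|
| k = 1 (equal SDs) | 2.0 | 2.86 | 4.0 | 6.67 |
| k = 0.75 | 1.56 | 2.21 | 3.08 | 5.12 |
| k = 0.5 | 1.25 | 1.70 | 2.33 | 3.82 |

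A simulation with equal SDs and an estimated slope gave 2.69, 3.82 and 6.39 at 12 per arm, and 2.73, 3.91 and 6.42 at 15 per arm (ρ = 0.3, 0.5, 0.7). Most of the gain therefore survives estimating the slope in groups this small.

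**Other ways of scoring the QALY** (equal SDs; ρ = 0.3, 0.5, 0.7):

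- Gain over baseline, ratio 2/(1 + ρ): 1.54, 1.33, 1.18
- Month-6 utility only, ratio 1/(1 − ρ²): 1.10, 1.33, 1.96

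**Illustration** (assumed: SD 0.2 at both visits, 15 per arm, ρ = 0.5, true month-6 gain 0.10, i.e. 0.25 × 0.10 = 0.025 QALY):

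- Raw SE = √(0.0625 × 2/15 × 0.04 × 3) = √0.00100 = 0.032
- Adjusted SE = √(0.0625 × 2/15 × 0.04 × 0.75) = √0.00025 = 0.016
- In simulation the estimate had the wrong sign in about 22% of trials raw and 6% adjusted.
- A one-SE baseline difference is 0.2 × √(2/15) = 0.073. It shifts the raw contrast by 0.25 × (1 + 0.5) × 0.073 = 0.027 QALY. If it goes against APAP, the expected raw difference is 0.025 − 0.027 = −0.002, while the adjusted one stays at 0.025.

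**Link with the planned utility ANCOVA.** On the two-point formula, the 0.25 × u0 part of the QALY is absorbed once u0 is a covariate. The arm coefficient for the QALY is then exactly 0.25 times the arm coefficient for u6 in the same model. The adjusted QALY estimate agrees with the planned utility analysis by construction; the raw one need not.

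**The case against.** The strongest reply is that the article is silent on adjustment rather than opposed to it. It specifies no unadjusted QALY test or interval, and a condensed article may leave such detail to a fuller plan. The section is mainly about how to measure and collect economic data for a later trial, its cost comparison is called preliminary, and Statistical analysis already asks for caution beyond the primary outcome. The utilities themselves do receive a baseline-adjusted analysis, of which, on the two-point formula, the adjusted QALY effect is only a rescaling.

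Most of this stands and limits the weight of the point. What remains is that the article does not leave the QALY method open: it names descriptive statistics, by arm, and attaches inferences to them.

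Three stronger readings are tempting and are not supported:

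- *The variance is at least doubled.* This needs a two-point area under the curve, similar SDs at both visits and a non-negative correlation. The documents state none of these, and the table shows ratios below 2 when they fail.
- *The QALY comparison is biased.* Over randomisation the raw difference is unbiased; chance imbalance affects a single trial's estimate, not its expectation.
- *The plan loses power.* No QALY hypothesis test is planned, so power is not a relevant criterion.

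**Conclusion.** The point holds as a minor improvement. Arm QALYs are to be summarised without the baseline utility already in hand, and conclusions drawn. If QALYs are area-under-the-curve quantities, chance baseline imbalance enters the raw comparison and can set it against the adjusted analysis of the same scores. The raw contrast is unbiased but imprecise: about 2.9, 4.0 and 6.7 times the adjusted variance at ρ of 0.3, 0.5 and 0.7 with equal SDs, and about 1.25 to 2.3 times for ρ of 0 to 0.5 if the baseline SD is half the month-6 SD. These sizes rest on an assumed two-point formula and on assumed utility SD ratios and correlations. None of the scenarios shown favours the raw contrast. The consequence is confined to a preliminary secondary analysis; the primary outcome and sample size are untouched.

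**What to change.** In Health economic analysis, keep the descriptive tables and add a sentence to this effect: any between-arm QALY difference is estimated in each cohort by linear regression of QALY on arm, baseline utility (CHU-9D in children, EQ-5D in adults) and the minimisation factors, reported with a confidence interval, and any statement about a QALY gain or loss rests on that estimate rather than on raw arm means.

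The cost is one extra regression per cohort, one degree of freedom for baseline utility and four for the minimisation factors (age group has two levels within a cohort). With 24 evaluable, 24 − (1 intercept + 1 arm + 1 baseline utility + 4 factors) = 17 residual degrees of freedom remain. No new data, visits or staff are needed. Participants without a baseline utility drop out of the model, but could not contribute an area-under-the-curve QALY without imputation in any case.

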## Discussion

Despite the wide availability of APAP, the well-known impact of SCD on cognitive development and pain, and the growing body of evidence for higher rates of OSA in this patient population, little has been done to evaluate the impact of an OSA intervention for SCD. The results of this study will inform clinicians about the utility of APAP in improving three domains that are important to patients: cognitive function; pain; and quality of life. The primary endpoint, processing speed, can have a widespread impact on domains of cognitive functioning and everyday life. Since there may be practice effects on some cognitive tests, performance may improve in both arms of the trial [18], which necessitates the use of a control group. We foresee that there will be improvements in cognitive means for both arms, but that the treatment group will show statistically greater improvements compared to the control group.

The natural history of sleep-disordered breathing in young children in the general population is to improve and a large randomised controlled trial of adenotonsillectomy did not find a statistically significant improvement in an executive function endpoint [55]. For endpoints including cognition and quality of life, the relative contributions of nocturnal desaturation, which particularly affects patients with sickle cell disease, and sleep apnoea with arousals are hotly debated. For patients with sickle cell disease, much less is known about the natural history of sleep-disordered breathing; there is no clinical consensus about where the threshold might be for an effect on cognition, pain or quality of life. Based on our previous findings that many patients with sickle cell disease have minimum oxygen saturation overnight, lower than the minimum documented in healthy asymptomatic children in the general population, we have elected to recruit both patients with evidence for obstructive sleep apnoea and those with more severe desaturation into this trial. This decision will allow comparisons of the magnitude of benefit across these groups.

### Trial status

The first participant was randomised on 23 March 2016. As of 30 March 2017, 30 have been randomised in the paediatric cohort and 28 in the adult cohort.

## Abbreviations

ANCOVA: Analysis of covariance
APAP: Auto-adjusting continuous positive airways pressure
ASL: Arterial spin labelling
BRIEF: Behavior Rating Inventory of Executive Function
CHU-9D: Child Health Utility-9D
CMS: Children’s Memory Scale
CPAP: Continuous positive airways pressure
CPT-III: Conner’s Continuous Performance Test-III
D-KEFS: Delis-Kaplan tests of Executive Function
DTI: Diffusion tensor imaging
EF: Executive function
e-NRS: Electronic numerical rating scale
EQ-5D: Euroqol-5D
FLAIR: Fluid‐attenuated inversion recovery
HbSS: Haemoglobin SS
HPLC: High performance liquid chromatography
HRQoL: Health-related quality of life
IEF: Isoelectric focusing
MRA: Magnetic resonance angiography
MRI: Magnetic resonance imaging
MS: Mass spectrometry
NHS: National Health Service
NOT: Nocturnal Oxygen Therapy
OAHI: Obstructive apnoea hypopnoea index
OSA: Obstructive sleep apnoea
PEDS-QL: Pediatric Quality of Life Inventory
POMS: Prevention of morbidity in sickle cell disease
QALY: Quality-adjusted life year
RD: Radial diffusivity
SCA: Sickle cell anaemia
SCI: Silent cerebral infarction
SpO2: Peripheral oxygen saturation
TBSS: Tract-based spatial statistics
WAIS-IV: Wechsler Adult Intelligence Scale-IV
WASI: Wechsler Abbreviated Scale of Intelligence
WISC-IV: Wechsler Intelligence Scale for Children-IV
WMS: Wechsler memory scale
